## 12 DATA MANAGEMENT

## **12.1 Data collection methods**

Initially, and in view of the current circumstances, the data will be collected on a paper observation notebook and then transmitted to the F-Widal-Lariboisière clinical research unit by photos or scanners and transcribed on e-CRF by a TEC.

## **12.2 Identification of data collected directly from FIUs that will be considered source data**

All data will be collected from the patient's medical record of all documents, including the patient collection form.

## **12.3 Right of access to source data and documents**

### **12.3.1 Access to data**

In accordance with GCPs:

- the sponsor is responsible for obtaining the agreement of all parties involved in the research in order to ensure direct access to all research locations, source data, source documents and reports for the purpose of quality control and audit by the sponsor,
- The investigators will make available to the persons in charge of monitoring, quality control, auditing research involving human persons, the documents and individual data strictly necessary for this control, in accordance with the legislative and regulatory provisions in force

### **12.3.2 Source documents**

Source documents, being defined as any original document or object that proves the existence or accuracy of a data or fact recorded during the research, will be kept for 15 years by the investigator or by the hospital in the case of a hospital medical record.

In the context of this research, the source documents are the medical records of each department in which the patient will have passed at some point in his or her care. The medical file, as well as the nursing and nursing assistant care file, paper or computerized version. The group A patient collection form will also be part of the source documents.

### **12.3.3 Data Privacy**

The persons responsible for quality control of research involving human beings (Article L.1121-3 of the Public Health Code) will take all necessary precautions to ensure the confidentiality of information relating to the research, to the persons who take part in it and in particular with regard to their identity and the results obtained.

These persons, in the same way as the investigators themselves, are subject to professional secrecy (under the conditions defined by Articles 226-13 and 226-14 of the Criminal Code).

During research involving humans and at the end of it, the data collected on suitable persons and transmitted to the sponsor by the investigators (or any other specialized stakeholders) will be made non-identifying.

They must not under any circumstances display the names of the persons concerned or their addresses in plain text.

The sponsor will ensure that each person who participates in the research has given his or her written consent for access to the individual data concerning him or her that is strictly necessary for the quality control of the research.

## 12.4 Data processing and retention of documents and data

### 12.4.1 Identification of the data controller and place of data processing

The creation of the database, the data entry, and the methods of protecting the confidentiality and security of the data, will be carried out according to the quality procedures in force at the Clinical Research Unit (CRU) Lariboisière – Saint Louis, under the responsibility of [name].

The analyses will be carried out under the responsibility of [name] using WINBUGS or R software.

The observations will be entered through a paper observation book. These CRFs will be entered by the investigator or a data entry technician, then transmitted to the CRU according to a predefined rhythm in the form of a photo or scanned and anonymised.

A TEC at the F-Widal CRU will transcribe it in the e-crf.

The database will be backed up on a daily basis. All of these operations will be carried out continuously, i.e. as the data is collected.

The computer control program for the consistency of information must be developed on the basis of a validation plan describing in detail the checks to be carried out for each variable (consistency of dates and deadlines, consistency of conditional variables, invalid values, bounds, missing data, compliance with criteria predefined in the protocol, etc.). "Inconsistent" data (not related to an input error) are edited once a month and sent to the TEC for verification of the information in the patient files.

### 12.4.2 Data Entry

Paper CRF : The data entry will be carried out by a TEC of the URC F-Widal-Lariboisière, [name] by staff dedicated to this purpose on data collection notebooks with non-identifying data

E-CRF: The entry of data that has been made non-identifying will be carried out on the cleanweb via a web browser.

## 12.5 Data ownership

AP-HP is the owner of the data and no use or transmission to a third party may be carried out without its prior consent.

## 13 STATISTICAL ASPECTS

### 13.1 Description of the planned statistical methods:

#### **Study size:**

This is a Bayesian study whose analysis will be based on the calculations of the a posteriori probabilities for a number of hypotheses. There is therefore no fixed sample size as in a frequentist analysis. The stop rules will be based on the probability calculations conditional on the data of an  $OR > 1$ , corresponding to a non-zero effect but also of an  $OR > 1.05$  corresponding to a more marked effect, but also on the probabilities of  $OR < 1$  ineffectiveness or of a marked deleterious effect  $OR < 0.95$  with respective probability thresholds set at 0.95, 0.80, 0.8, 0.75. Vague priors but adapted to Bayesian studies using ORs will be used. The maximum size of the study is set at  $N=500$  patients (based on the size of a frequentist study with a power of 80% to demonstrate a difference of 10%

between the 2 groups (i.e. 25% vs 15%). The simulations carried out show a high probability that the study will be conclusive after the inclusion of less than 300 patients.

### ***Descriptive statistical analysis:***

For each group: The descriptive statistical analysis will include for each quantitative parameter: mean, standard deviation, minimum, maximum, median and quartiles, number of missing values. The qualitative parameters will be expressed by the frequency of distribution.

Bayesian statistics:

### ***Main criterion:***

The posterior probabilities of the primary endpoint will be calculated using different types of priors (non-informative or vague).

The following posterior probabilities will be calculated:

P (OR>1), corresponding to a non-zero effect of the prone position.

P (OR>1.05) corresponding to an effect that is already clinically interesting.

P (OR<1) corresponding to inefficiency of the prone position.

P (OR < 0.95) corresponding to a deleterious effect of the prone position.

The thresholds considered particularly interesting for the a posteriori probabilities described below are respectively equal to 0.95, 0.80, 0.8, 0.75.

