### **2.3 Description of the population to be studied and justification for its choice**

Adult COVID-19 patients (PCR or typical CT imaging), not intubated, requiring oxygen therapy at a rate of at least 3L/min to get a peripheral saturation greater than or equal to 95%.

We observed during the recent management of patients in the context of the current COVID epidemic that oxygen supply at more than 3L/min was associated with a high proportion of deterioration with severe respiratory distress.

Thus, among patients admitted to hospital in China for COVID-19 pneumonia, 26% are secondarily admitted to intensive care, among which 50% of patients require mechanical ventilation. However, only 80% of patients were oxygen-requiring in the Guan et al. series. Including patients requiring at least 3L/min of oxygen, some of which will be included in the intensive care unit and already on high-flow oxygen therapy, we estimate that 20% of the patients included will require mechanical ventilation or die in the arm without prone positioning.

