## 6.1 Research Timeline

### 6.1.1 Inclusion visit.

For 18 months following the validation of the ethics committee, patients meeting the criteria and admitted to the COVID ward or intensive care in the 21 centers within the 11 hospitals in France and Mexico referenced for this study will be offered to participate in the study orally after verification of the inclusion and non-inclusion criteria and then a written consent will be collected. Notification of the patient's participation in this study will be listed in the patient's medical record.

We will collect:

**Socio-demographic data:** age, sex, weight, height, date of onset of symptoms, date of hospital admission

**Constants:** systolic blood pressure (SBP), diastolic blood pressure (DBP), heart rate (HR), body temperature, respiratory rate (RH), oxygen saturation, oxygen therapy flow.

Collection of the date of the last chest CT scan before inclusion with percentage of lung parenchyma involvement on CT images. Chest CT scan is not required for the study if the patient has not had one.

**Biology:** white blood cell counts, serum creatinine, D-Dimer, AST, and ALT (liver enzymes). This assessment will be collected, if it exists, made within the usual framework.

**Medical history:** chronic respiratory disease, cardiovascular disease, liver disease, diabetes and cancer or hematopathy under treatment.

Randomization will be done following the collection of written consent, via Cleanweb software.

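### The primary OR that drives every stopping decision is defined with no baseline covariates named, although prognostic severity measures are collected at inclusion; adjusting for them is cheap and gives a small gain.

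*Protocol*

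**What the plan says.** Protocol 13.1, Main criterion, reads "The posterior probabilities of the primary endpoint will be calculated using different types of priors (non-informative or vague". It lists four posterior probabilities of the OR, with thresholds at 1, 1.05 and 0.95. It names neither a model nor a covariate. Under the stopping criteria in the same section, looks come every 50 patients, and efficacy or harm stops are allowed after the second.

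Other sections bear on this:
- **6.1.1, Inclusion visit:** age is recorded, as are "respiratory rate (RH), oxygen saturation, oxygen therapy flow". CT extent and laboratory values are recorded only when routine care has produced them.
- **2.3, Population:** "oxygen supply at more than 3L/min was associated with a high proportion of deterioration with severe respiratory distress". Section 2.1.1 says much the same.
- **5.2, Recruiting centres:** wards and ICUs both recruit, the latter including patients already on high-flow oxygen or NIV.
- **13.1, Secondary analyses:** age over 70, baseline NIV or high-flow, and ICU status appear only as subgroups.
- **Stratification:** the synopsis gives ICU status; 5.3.3 gives centre.
- **13.1, Study size:** "The maximum size of the study is set at" 500, "based on the size of a frequentist study with a power of 80% to demonstrate a difference of 10" points, "between the 2 groups (i.e. 25% vs 15" percent.

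**The concern.** The protocol recognises that severity at entry predicts intubation or death and records it, but does not place it in the analysis that decides the trial. Two things are at stake.

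The first is efficiency. In a population of mixed severity, a treatment comparison that ignores strong predictors is less powerful than one that uses them.

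The second is the integrity of the stopping decision. The rules act on the posterior of one particular OR. The adjusted and unadjusted ORs are different quantities with different posteriors. In an open-label trial with repeated looks, leaving the choice unstated means it could be made after data are seen. At 100 patients, a chance difference in severity between arms can carry the unadjusted posterior over a threshold. Stratifying by centre does not prevent this, and stratifying by ICU status does not balance age, respiratory rate or oxygen flow within a ward or an ICU.

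**Working it through.** **1. The plan's own figure.** Inputs: 25% vs 15% and 80% power (Study size). Two-sided 5% and 1:1 allocation are assumptions, since neither is stated.

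n per arm = [1.960·√(2·0.20·0.80) + 0.842·√(0.25·0.75 + 0.15·0.85)]² / 0.10² = (1.109 + 0.472)² / 0.01 ≈ 250, so 500 in total. The cap is reproduced, with power 80.0%.

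**2. Gain at fixed N = 500.** Model: logit(risk) = a + t·arm + s·x, where x is a standard normal severity score. a and t are set so that marginal risks stay at 25% and 15%. There were 6,000 simulated trials per row (simulation error about 0.5 point). The adjusted fit also carries two pure-noise covariates.

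| s | AUC | Unadjusted | Adjusted | Gain (points) |
|---|---|---|---|---|
| 0.5 | 0.64 | 79.8% | 81.0% | 1 |
| 0.75 | 0.69 | 79.6% | 82.9% | 3 |
| 1.0 | 0.75 | 79.9% | 84.7% | 5 |
| 1.25 | 0.79 | 79.9% | 87.3% | 7 |

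At AUC 0.82 the gain is 9 points. Section 2.3 uses a different control rate: "we estimate that 20% of the patients included will require mechanical ventilation or die in the arm without prone positioning". Keeping the 25:15 ratio gives 20% × 15/25 = 12%, and the gain over AUC 0.64 to 0.79 is then 2 to 8 points.

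**3. Gain under the protocol's sequential rules.** Looks every 50 patients; efficacy from 100 patients if P(OR>1) > 0.95 or P(OR>1.05) > 0.8; harm from 100 if P(OR<0.95) > 0.75; futility from 200 if P(OR>1) < 0.1. The prior is near-flat and OR>1 is taken as benefit, as the protocol does. There were 1,500 trials per row (error about 0.5 point near 96%).

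| AUC | Power, unadjusted → adjusted | Mean N | False efficacy at 20% vs 20% |
|---|---|---|---|
| 0.64 | 96.6% → 96.4% | 143.5 → 140.3 | 33.7% → 33.7% |
| 0.75 | 95.3% → 96.8% | 142.8 → 139.1 | 35.3% → 37.1% |
| 0.82 | 96.1% → 97.8% | 148.5 → 133.0 | 33.9% → 37.5% |

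The power gain is about 0 to 2 points. With P(OR>1) > 0.95 as the only efficacy rule it is about 0 to 4.5 points. A separate run of 3,000 trials per setting agreed: about 96% vs 97% power, about 2 to 10 fewer patients on average, and 35–37% false efficacy stops either way. In 15–26% of its null trials the two analyses reached different verdicts.

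**4. The first permitted stop.** 50 per arm, 20% risk in both arms, both efficacy rules, 8,000 trials per setting, total severity SD 0.6, 0.9 and 1.2 on the logit scale (AUC about 0.66, 0.72 and 0.78).
- All trials: about 17–19% cross an efficacy threshold with either analysis.
- The fifth of trials where chance severity most favours the prone arm: about 28%, 34% and 35% unadjusted, against 19%, 20% and 19% adjusted.
- The two analyses disagree on stopping in about 6%, 8% and 10% of trials.

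**5. Sparse events.** Expected events at 100 patients: 50 × 0.25 + 50 × 0.15 = 20. With oxygen support in three categories, the adjusted model has about five slopes (treatment, age, respiratory rate, two oxygen contrasts), or 20/5 = 4 events per slope.

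**6. What the thresholds mean.** Oriented so that benefit exceeds 1, the marginal OR for 25% vs 15% is (0.25/0.75)/(0.15/0.85) = 1.89. The conditional OR giving the same marginal risks is 1/0.516 = 1.94 at AUC 0.64 and 1/0.457 = 2.19 at AUC 0.79. The null value 1 is shared, but 1.05 and 0.95 do not describe the same effect on the two scales.

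**The case against.** **Silence is not a decision.** A reader might infer that the protocol has chosen an unadjusted analysis. It has not: it never says unadjusted, and a covariate list is commonly left to a statistical analysis plan, which may exist. That stands, and is why the point is framed as what 13.1 fails to name. It does not dispose of the matter, because the OR is part of the stopping rule, and 13.1 (Manage changes to the initial strategy analysis plan) foresees a specific plan only if the criteria change.

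**The power loss is small.** A reader might carry the 1 to 7 points over to the trial as it will be run. The documents do not support this. Those points belong to a single two-sided 5% test at 500, whereas the protocol stops on looser thresholds at repeated looks and says "There is therefore no fixed sample size as in a frequentist analysis". There the gain is 0 to 2 points. This stands in full.

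**The strength is assumed.** No AUC is given, and the simulations use well-behaved covariates with a correctly specified model. This also stands.

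**Adjustment does not cut false early stops.** With oxygen in three categories at 50 per arm, crossings under no effect were 17.2%, 18.0% and 16.8% unadjusted and 17.9%, 19.4% and 18.2% adjusted. So the average is not improved; the benefit is confined to trials with a chance imbalance.

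**Stratification may already cover ICU status.** The synopsis says so, though 5.3.3 names centre only. Even if it applies, severity within each setting is left unbalanced.

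**A marginal OR is a legitimate target.** Agreed. The described OR is not invalid, and moving to a conditional one requires saying what the thresholds refer to.

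**Conclusion.** The point holds as a low-cost improvement, not as an error that invalidates the design. Section 13.1 names no covariate for the primary OR although prognostic measures are collected at inclusion and the population is of mixed severity.

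Assuming AUC 0.64 to 0.79, 1:1 allocation and near-flat priors on the treatment effect, adjustment is worth about 1 to 7 points for the calculation behind the cap and about 0 to 2 points under the sequential rules, with a slightly smaller expected sample size. It leaves the average false-efficacy rate materially unchanged. The stronger reason to act is that the two analyses give different verdicts in a noticeable share of null trials (6–10% at the 100-patient look, 15–26% over the whole trial), so the choice must not be open once looks begin.

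**What to change.** In 13.1, Main criterion, state that the primary OR at every look comes from one Bayesian logistic model, fixed before the first look, with treatment, age, baseline respiratory rate and baseline oxygen support. Oxygen support should be in categories, because litres by mask and by high-flow are not comparable. Use weakly informative priors on the covariate slopes, given about 20 events at 100 patients. State that the thresholds 1, 1.05 and 0.95 refer to the conditional OR. Report the unadjusted OR and the standardised risk difference alongside. Leave out CT extent and laboratory values, which are not available for every patient. If a statistical analysis plan already names covariates, bring the two documents into line.

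Cost: a few sentences and no new data collection. The downsides are an OR that is conditional on the covariates and a somewhat more complex model at the early looks.

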### ***Secondary Criteria***

For each parameter, the a posteriori probabilities will be described using different types of priors (non-informative or vague). The 95% credibility intervals will be calculated.

### ***Secondary analyses***

An analysis of the following subpopulations is planned a priori:

- Age >70 years
- Patients with NIV or high-flow oxygenation at baseline
- Patients included in intensive care or not

### ***Statistical criteria for stopping the search.***

Interim analyses will be done every 50 patients (followed up to the primary endpoint).

The study may be stopped for efficacy after the 2nd interim analysis, if one of the 2 conditions below is met:

P( OR>1) >0.95

P (OR>1.05) >0.8

The study may be stopped after the 2nd interim analysis for safety if P (OR< 0.95) >0.75

The study may be stopped for futility after the 4th interim analysis

P( OR>1) < 0.1

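### The either/or efficacy stop lets the laxer condition, P(OR>1.05)>0.8, decide every time: about 35% of trials of an ineffective intervention reach it, and the protocol does not report this

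*Protocol*

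**What the plan says.** The rule is in Protocol section 13.1, under *Statistical criteria for stopping the search*. Interim analyses take place after each 50 patients who have completed the primary endpoint. On efficacy: "The study may be stopped for efficacy after the 2nd interim analysis, if one of the 2 conditions below is met". The two conditions are P(OR>1)>0.95 and "P (OR>1.05) >0.8". Two further rules follow: "The study may be stopped after the 2nd interim analysis for safety if P (OR< 0.95) >0.75", and "The study may be stopped for futility after the 4th interim analysis", the latter when P(OR>1)<0.1.

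Under *Main criterion*, the first quantity is "P (OR>1), corresponding to a non-zero effect of the prone position" and the second is "P (OR>1.05) corresponding to an effect that is already clinically interesting". The synopsis and *Study size* give the same thresholds and describe OR>1.05 as the more pronounced effect. *Study size* calls for vague priors and caps the trial at 500, taken from a frequentist calculation with 80% power for 25% vs 15%. It adds: "The simulations carried out show a high probability that the study will be conclusive after the inclusion of less than 300 patients". No section says how often the efficacy criterion would be met if prone positioning had no effect.

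**The concern.** When either of two conditions is enough, the easier one sets the standard. The wording suggests that the 1.05 condition adds a demand for a larger effect. However, lowering the required probability from 0.95 to 0.80 gives away far more than moving the margin from 1.00 to 1.05 takes back. If so, the 0.95 threshold has no function, and the efficacy stop can be triggered repeatedly, at up to nine looks, on evidence well short of 95% posterior probability. The trial's main conclusion rests on this rule, so readers need to know how often it fires with no effect present.

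**Working it through.** **Inputs.** From the protocol: either/or connector; thresholds 0.95 and 0.80; looks every 50 patients; efficacy and safety stops from the 2nd look; futility from the 4th; maximum 500; rates 25% vs 15% (*Study size*); expected control rate 20% (section 2.3); vague prior. Assumed because not stated: 1:1 allocation, OR>1 meaning benefit, and action whenever a criterion is met.

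**Step 1. Reproduce the 500.** With two-sided alpha 0.05 (assumed) and 80% power:

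n per arm = [1.96·√(2·0.20·0.80) + 0.842·√(0.25·0.75 + 0.15·0.85)]² / 0.10² = (1.109 + 0.472)² / 0.01 ≈ 250, so 500 in total. The figure reproduces. A one-sided 5% calculation would give 394.

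**Step 2. Which condition is easier?** Let m and s be the posterior mean and SD of log OR. Under a vague prior, s is close to the standard error.

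- P(OR>1)>0.95 needs m > 1.645·s.
- P(OR>1.05)>0.80 needs m > ln(1.05) + 0.842·s = 0.0488 + 0.842·s.

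The second is easier whenever s > 0.0488/(1.645 − 0.842) = 0.061.

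With a common event rate p, s ≈ √[4/(N·p·(1−p))]. At N=500 this is 0.25, 0.22 and 0.21 for p = 15%, 20% and 25%. Reaching s = 0.061 would take about 5,800 patients (p=25%) to 8,500 (p=15%). In the simulations below, no look met the 0.95 condition without also meeting the 0.80 condition.

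**Step 3. The bar that actually operates (p=20%).**

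| N | s | m needed by the 0.80 condition | P(OR>1) at that point | observed OR needed: 0.80 condition / 0.95 condition |
|---|---|---|---|---|
| 100 | 0.500 | 0.0488+0.842·0.500 = 0.470 | Φ(0.94) = 0.83 | 1.60 / 2.28 |
| 500 | 0.224 | 0.0488+0.842·0.224 = 0.237 | Φ(1.06) = 0.86 | 1.27 / 1.44 |

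**Step 4. What the 1.05 margin means.** From a 25% control rate, odds of 0.3333/1.05 = 0.3175 give 24.1%, a difference of 0.9 points. The sizing effect, 25% vs 15%, is OR 0.3333/0.1765 = 1.89.

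**Step 5. The whole rule under no effect.** Simulated trials, 25 patients per arm per look, safety and futility stops on:

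| Setting | Efficacy criterion reached |
|---|---|
| Either/or rule from N=100, event rates 15–25%, near-flat, Jeffreys or uniform priors | 35–36% |
| Same, first stop at N=150 (strict reading of *after the 2nd*) | 32–34% |
| N(0,1) prior on log OR, from N=100 | 32.5% |
| N(0, SD 0.5) prior, no longer vague | about 27% |
| P(OR>1)>0.95 alone, from N=100 | about 14% |

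Combining the N(0,1) prior with a first stop at N=150 gives about 30%. Ignoring the safety stop raises the either/or figure to 36–39%.

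**Step 6. Stopping before 300.** Under no effect, about 64–65% of trials stop before 300 patients: about 29 points for efficacy and the rest essentially for safety. At 25% vs 15%, about 92% stop before 300 as written, and about 72–74% would do so with P(OR>1)>0.95 as the only efficacy condition.

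**The case against.** The strongest reply is that this is a Bayesian design. It promises no type I error, it prints both thresholds openly, and it says only that the study may be stopped. Much of that stands.

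- A reader might infer that the trial breaches its alpha. It does not, because none is stated.
- A reader might infer that 35% of useless interventions would be declared effective. The text defines no declaration of success, and all four posterior probabilities are to be calculated. The 35% is the chance that the criterion is reached, and it becomes a stopping rate only if acted on.
- A reader might infer that the lower threshold is concealed. It is printed beside the 0.95 wherever the thresholds appear.
- A reader might infer that the statement about concluding before 300 patients is mostly an artefact of the lax condition. It is not: at the design effect the 0.95 condition alone still ends about 72–74% of trials by then. Of the early stops under no effect, fewer than half are for efficacy.
- The prior is not specified numerically, and a tighter one lowers the figure, to about 27% at SD 0.5 on log OR. That would not be a vague prior.

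What the reply does not answer is the redundancy. On purely Bayesian terms, a plan that lists a 0.95 posterior requirement which can never operate, and treats the weaker condition as the more demanding, does not set the standard it appears to set. The protocol also uses frequentist power for its size and cites simulations for its expected duration, so a null operating characteristic is a fair thing to ask of it.

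**Conclusion.** The point holds as a badly calibrated decision rule and should be corrected. Up to N=500 the 0.95 condition is inoperative. The operating bar is P(OR>1) of about 0.83 to 0.86, and the efficacy criterion is reached in about 35% of trials with no effect (32–36% across vague priors and first-look readings, about 30% at the lowest combination tried), against about 14% for the 0.95 condition alone. This rests on 1:1 allocation, OR>1 meaning benefit, a vague prior, the rule being acted on when met, and the existing safety and futility stops applying. The documents support calling this an unreported operating characteristic. They do not support calling it a violated error rate. The statement about concluding before 300 patients is not shown to be wrong, but it is incomplete without the corresponding null results.

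**What to change.** In section 13.1 and the synopsis, remove P(OR>1.05)>0.8 as a stopping criterion and report that probability descriptively. Use one efficacy rule, P(OR>1)>c, with c calibrated by simulation over all planned looks. State the prior used, the resulting null efficacy-stop rate, and the share of trials stopping before 300 both under no effect and under 25% vs 15%. Two workable examples, with the existing safety and futility stops kept:

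| Rule | Efficacy stop under no effect | Success at 25% vs 15% | Mean N at 25% vs 15% | Mean N under no effect |
|---|---|---|---|---|
| c = 0.985 at every look from N=100 | about 5% | about 80% | about 290 | about 345–350 |
| c = Φ(2.05·√(500/N)), i.e. 0.980 at N=500 | about 2.6% | 78–79% | about 375 | about 355–360 |

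The second is closer to the two-sided 5% that reproduces N=500. The choice of calibration belongs to the trial team, but it should be stated and justified.

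The cost is a change of wording, a rerun of the simulations and the amendment procedure of section 15.7. The 500 maximum is unchanged. The price is fewer very early efficacy stops: at 25% vs 15% the rule as written has a mean N of about 145 and about 96% success, so expected size rises and success falls to the planned level of roughly 80%.
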